#### Economic evaluation

*Quality of life* will be determined with the five-level version of the EuroQol (EQ-5D-5L), a self-report questionnaire assessing the health related well-being of participants [61]. The questionnaire consists of five items: mobility, self-care, daily activities, discomfort and mood state. Each item has five response categories ranging from ‘no problems’ to ‘a lot of problems’ [62]. Furthermore, this scale contains a visual analogue scale concerning health state. The EQ-5D-5L health states will be converted to utility scores using the Dutch tariff. Quality-adjusted life-years (QALYs) will be calculated by multiplying the utility of a specific health state by the time spent in that health state. Changes in health states between measurements will be linearly interpolated. The EQ-5D-5L holds acceptable levels of content validity [63] and has demonstrated valid redistribution, reduced ceiling, and improved discriminatory power and convergent validity compared to the EQ-5D-3L [64].

*Health care utilisation* and *productivity losses due to illness* will be measured using an adapted version of the Trimbos and iMTA Questionnaires on Costs Associated with Psychiatric Illness (TiC-P), a self-report questionnaire consisting of two different parts that can be administrated separately [65]. Part I will be used to assess the participants’ healthcare utilisation and medication use. Part II (short form Health and Labor Questionnaire; SF-HLQ) consists of 11 items measuring lost productivity costs resulting from absenteeism (being absent from work because of illness) and presenteeism (being present at work while ill which may lead to reduced efficiency).

#### Engagement and usage measures for bCBT

Activities on the platform such as number of visits, time in-between logins and number of messages exchanged between patient and therapist, will be assessed through track and change functionalities (log files). Data on how patients use online modules (frequency, duration, order, completion), how they rate them and to what extent they adhere, will also be obtained through usage statistics on the Moodbuster online treatment platform.

Patients receiving the blended treatment will as part of the treatment protocol additionally fill out the PHQ-8 at the end of each module, for monitoring treatment outcome (i.e., all items on the PHQ-9 scale except the ninth item). As this data is being gathered in a self-administered fashion and direct action on positive responses on the ninth item inquiring “thoughts that you would be better off dead or of hurting yourself in some way” is not feasible, it was chosen to exclude this item. Patients are instructed to use existing services of the mental health care organisations when they feel the need to contact a doctor or a therapist outside working hours. The PHQ-8 has similar operating characteristics as the PHQ-9 (sensitivity, specificity, and positive predictive value), regardless of the threshold [38].

### Sample size

For the European study as a whole, the sample size calculation is based on the non-inferiority design and calculated for the primary clinical outcome symptoms of depression. The non-inferiority margin was set at ∆Cohen’s d = 0.20, which is a conservative estimate of the subjective minimal important difference that is noticeable by patients [66]. To determine that there is no difference between blended depression treatment and TAU on the primary clinical outcome, a total of 1052 patients is required to be 90 % certain (power of .90) that the lower limit of the two sided 95 % confidence interval will be above the non-inferiority limit of Cohen’s *d* = -0.2. To allow for expected drop-out and variation between settings, the total number of participants to be recruited will be 1200.

For the current trial in the Netherlands we aim to include 156 participants (78 per arm). This sample size will be sufficient to be 80 % sure (i.e. power = 1-ß = 0.80) that the lower limit of a one-sided 95 % confidence interval (or equivalently a 90 % two-sided confidence interval) will be above a non-inferiority limit of -0.4 if we assume that there is no difference between the standard and blended depression treatment. A margin of 0.4 was judged acceptable, as this range of small to moderate difference in effect size will not result in clinically important differences [67].

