### Randomisation and blinding

Randomisation will take place at an individual level stratified by mental healthcare centre. The allocation will be conducted centrally at the VU Amsterdam by an independent team of researchers which is not involved in the trial. A computerised random number generator [39] is used to produce the allocation scheme with an allocation ratio 1:1. Subjects will be randomised into two groups: bCBT or TAU. The allocation is concealed, researchers and clinicians will be unknown to the randomisation scheme. Blinding for the treatment is not possible as it will be clear to both therapists and patients when the treatment is blended or not. However, the assessor conducting the M.I.N.I. at follow-up will be blinded to treatment status. The flowchart of the study is presented in Fig. 1, according to CONSORT guidelines [40].

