### Planned statistical analyses

In a non-inferiority trial, the study objective should be achieved in both the intention to treat and per-protocol population [68]. Analysis will be based on intention to treat (ITT) design, including all participants randomised in the study. Participants will be encouraged to provide assessment data, regardless of treatment adherence. Additionally, per-protocol (PP) analysis will be conducted, including only participants who followed the treatment protocol of the assigned treatment. Non-inferiority should be demonstrated also in the PP analysis, because ITT tends to dilute differences [69]. All analyses will be performed using the Statistical Package for the Social Sciences (SPSS), version 20.0.

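### The 80 % power stated for 156 patients is the unadjusted, complete-data power of one analysis; it allows for no loss and does not cover the requirement that non-inferiority hold in both ITT and PP

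*Protocol article*

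**What the plan says.** The Sample size section of the protocol article treats two studies in turn.

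- **European study.** 1052 patients are required for 90 % power with a margin of 0.2 and a two-sided 95 % interval. A separate step follows: "To allow for expected drop-out and variation between settings, the total number of participants to be recruited will be 1200".
- **Dutch trial.** "For the current trial in the Netherlands we aim to include 156 participants (78 per arm". Of this number the section says "This sample size will be sufficient to be 80 % sure (i.e. power = 1-ß = 0.80". The criterion uses a one-sided 95 % limit, treated as the same thing as a two-sided 90 % interval, which "will be above a non-inferiority limit of -0.4". The calculation takes the two treatments to be equally effective. No loss rate is given, and no second, larger recruitment number.

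Randomisation and blinding specifies an "allocation scheme with an allocation ratio 1:1".

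Planned statistical analyses sets the success rule. The objective is to be met in both populations, and the section repeats the point: "Non-inferiority should be demonstrated also in the PP analysis, because ITT tends to dilute differences". The PP set is restricted to those who followed the protocol of their assigned treatment. Its expected size is not stated.

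The Clinical evaluation section plans a mixed model on the 3-, 6- and 12-month outcomes with the baseline score as covariate. No baseline-outcome correlation is given anywhere, and the sample size section does not mention one.

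**The concern.** The section separates required from recruited patients for the European study but not for the Dutch trial, which is part of it. If 156 is already the bare requirement, any loss from the analysed set lowers the power below the stated figure, unless something else compensates.

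The success rule is also stricter than the calculation. Power was computed for one comparison, whereas the plan asks for two to succeed. The second is made in a subset that any non-adherence over the 19–20 weeks of treatment will make smaller.

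At stake is how the result is read. A reader who takes 80 % as the chance of meeting the trial's criterion under true equality may give too much weight to a failure to show non-inferiority, when limited precision could explain it.

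**Working it through.** **Inputs from the protocol article.** Margin 0.4 on the Cohen's *d* scale (so SD = 1), one-sided α = 0.05 (z = 1.645), power 0.80 (z = 0.842), true difference 0, 1:1 allocation, 78 per arm.

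**Step 1: reproduce the Dutch figure.**
n per arm = 2(1.645 + 0.842)² / 0.4² = 77.3, rounded up to 78; total 156.
Power at 78 per arm = Φ(0.4·√(78/2) − 1.645) = Φ(0.853) = 0.803 (0.800 with the noncentral *t*).
So 156 is the uninflated requirement with no reserve.

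**Step 2: reproduce the European figure.**
2(1.960 + 1.282)² / 0.2² gives just over 525, rounded up to 526 per arm; total 1052. The step to 1200 is an allowance of 1 − 1052/1200 = 12.3 % of those recruited.

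**Step 3: single-analysis power under loss, no baseline adjustment.** The loss rates are assumptions. The 12.3 % is a benchmark only, because it covers drop-out and variation between settings together. Power = Φ(0.4·√(n/2) − 1.645), with n = 78(1 − loss).

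| Assumed loss | n per arm | Power |
|---|---|---|
| 0 % | 78 | 0.803 |
| 10 % | 70.2 | 0.766 |
| 12.3 % | 68.4 | 0.756 |
| 20 % | 62.4 | 0.722 |
| 25 % | 58.5 | 0.698 |

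**Step 4: joint power for ITT and PP, no baseline adjustment.** Assume that PP is a random subset of the evaluable patients and that the true difference is 0 in both sets. The two test statistics are then bivariate normal with correlation √(n_PP/n_ITT), and joint power is the probability that both exceed 1.645.

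- No ITT loss, PP at 90, 80 or 70 % of patients: 0.744, 0.697, 0.646.
- PP at 80 % of evaluable patients, with 12.3, 20 or 25 % loss: 0.643, 0.606, 0.580.

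**Step 5: what baseline adjustment could recover.** With correlation r between baseline and outcome, the residual SD is √(1 − r²), so power = Φ(0.4·√(n/2)/√(1 − r²) − 1.645). ITT power returns to the complete-data value when r² equals the loss: r = 0.35 at 12.3 %, 0.45 at 20 %, 0.50 at 25 %. With an assumed r = 0.5:

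| Assumed loss | ITT power | Joint power (PP 80 % of evaluable) |
|---|---|---|
| 0 % | 0.892 | 0.81 |
| 12.3 % | 0.85 | 0.76 |
| 25 % | 0.803 | 0.70 |

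With r = 0.3 and PP at 80 %, joint power is 0.735 with no loss and 0.644 at 20 % loss.

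**The case against.** The strongest reply is that the calculation is correct and that the planned analysis is more efficient than the formula behind it. Three features support this:

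- ITT keeps everyone randomised and seeks assessments whether or not the patient adheres, so stopping treatment is not loss from ITT.
- The mixed model uses three follow-up times, so a patient who misses one still contributes. Step 3 removes each lost patient entirely and is pessimistic in that respect.
- The baseline covariate reduces residual variance. With r = 0.5, ITT power is still 0.80 at 25 % loss.

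The PP fraction is also a reviewer's assumption. Applying 80 % on top of loss treats non-adherence and missing data as separate, although they may overlap.

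All of this stands, and it rules out two tempting readings. A reader might infer an arithmetic error; there is none, since both 156 and 1052 reproduce. A reader might also infer that 80 % holds only if all 156 are analysed, or that the true ITT power must be lower. Without a stated correlation, the documents do not settle the direction for ITT.

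The reply does not show that the stated 80 % applies to the dual criterion. The sample size section relies on no correlation. Even at r = 0.5 with PP at 80 %, joint power is above 0.80 with no loss but 0.76 at 12.3 % loss. Nor is this merely detail that an article leaves to a fuller document: the article itself states the number, the power and the dual requirement.

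**Conclusion.** The point holds in a limited form. The stated 80 % is the unadjusted, complete-data power of one analysis. It carries no loss allowance, unlike the European figure beside it, and it does not describe the chance of meeting the stated ITT-and-PP criterion.

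On the sample size section's own assumptions, single-analysis power is about 0.77 to 0.70 for 10 to 25 % loss. Joint power is about 0.74 to 0.65 with complete ITT data and PP at 90 to 70 %, and about 0.64 to 0.58 at 12.3 to 25 % loss with PP at 80 % of evaluable patients. Baseline adjustment at an assumed r = 0.5 would raise the last range to about 0.76 to 0.70.

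Every figure below the stated 80 % depends on a loss rate or PP fraction that the documents do not give. In particular, 12.3 % should not be read as an expected Dutch drop-out rate. None of these figures should be quoted as the trial's actual power.

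**What to change.** Keep 156 and rewrite the Dutch paragraph of the Sample size section to:

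1. state that 80 % is the unadjusted, complete-data power for one analysis;
2. state the expected loss, the expected PP fraction and any baseline-outcome correlation relied on;
3. replace the single 80 % figure with the resulting ITT power and the joint ITT and PP power, each labelled with its assumptions.

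The values should be the sponsor's own; the ranges above only illustrate the size. The cost is one rewritten paragraph and probably a less favourable stated power. No extra patients and no change to the analysis are needed.

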### Planned statistical analyses

In a non-inferiority trial, the study objective should be achieved in both the intention to treat and per-protocol population [68]. Analysis will be based on intention to treat (ITT) design, including all participants randomised in the study. Participants will be encouraged to provide assessment data, regardless of treatment adherence. Additionally, per-protocol (PP) analysis will be conducted, including only participants who followed the treatment protocol of the assigned treatment. Non-inferiority should be demonstrated also in the PP analysis, because ITT tends to dilute differences [69]. All analyses will be performed using the Statistical Package for the Social Sciences (SPSS), version 20.0.

#### Economic evaluation

We will perform an economic evaluation from societal perspective, conducting a cost-effectiveness analysis (CEA) and cost-utility analysis (CUA). The CEA will be based on treatment response, defined as a 50 % pre-post reduction of QIDS-SR depressive symptoms [49]. The CUA will be conducted using quality adjusted life years (QALYs) as a generic measure of health gains. Multiple imputation using chained equations (MICE) will be used to impute missing cost and effect data. Predictive Mean Matching will be used to account for the skewed distribution of costs [70]. Variables that will be included in the multiple imputation model are variables related to missingness, variables related to costs and effects at 12 months of follow-up and all variables included in the analysis model. The number of imputations will be increased until the fraction of missing information (FMI) is 5 % or less [70]. The completed datasets will be analysed separately and pooled using Rubin’s rules [71].

Multilevel analyses with adjustment for mental health care institution will be done to estimate differences in costs and effects between bCBT and TAU while correcting for potential effect modifiers and confounders. Incremental cost-effectiveness ratios (ICERs) will be calculated by dividing the difference in costs by the difference in effects. Bias-corrected and accelerated bootstrapping with 5000 replications will be used to estimate statistical uncertainty. Bootstrapped cost-effect pairs will be plotted on cost-effectiveness planes (CE planes) to visualize the uncertainty surrounding the ICERs. Moreover, for decision-making purposes cost-effectiveness acceptability curves will be estimated showing the probability that bCBT is cost-effective in comparison with TAU at a range of different ceiling ratios. Finally, to test the robustness of our findings, sensitivity analyses will be performed. First, the economic evaluation will be conducted from a healthcare perspective. Secondly, a per protocol analysis will be done in which only participants completing the bCBT treatment protocol will be included.

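### The stopping rule for imputations is set on the fraction of missing information, which has a floor that adding imputations does not lower

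*Protocol article*

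**What the plan says.** The rule is in the protocol article, Planned statistical analyses, Economic evaluation. Missing data are handled as follows: "Multiple imputation using chained equations (MICE) will be used to impute missing cost and effect data", with predictive mean matching for the skewed costs. The number of imputations is then fixed by a stopping rule: "The number of imputations will be increased until the fraction of missing information (FMI) is 5" % or less. Pooling is by Rubin's rules: "The completed datasets will be analysed separately and pooled using" those rules.

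The limit is on FMI itself. The text does not mention loss of efficiency, FMI/m or Monte Carlo error, and it gives no maximum number of imputations and no fallback. No other section restates or corrects the rule.

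**The concern.** FMI is a property of the data and the imputation model. It measures how much of the variance of an estimate comes from not having observed some of the values. More imputations estimate that share more precisely but do not reduce it. What m does reduce is the extra variance from using a finite number of imputations, roughly FMI/m relative to infinitely many. The rule asks m to control a quantity that it does not control.

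An analyst who follows the text and finds FMI levelling off above 5 % has no instruction. They must depart from the plan, or stop at a small m where a noisy estimate happens to fall below 5 %. A reader might also take the sentence as an assurance that missing data will contribute no more than 5 % of the variance, which adding imputations cannot give. Cost-effectiveness is part of the primary objective (Trial objectives), so the handling of missing data there should be workable as written.

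**Working it through.** **Inputs.** The 5 % is a chosen threshold, so there is no derived figure to reproduce. From Sample size: "we aim to include 156 participants (78 per arm"), and, for the European study, 1052 required and 1200 recruited ("To allow for expected drop-out and variation between settings, the total number of participants to be recruited will be 1200"). The implied allowance is 1 − 1052/1200 = 0.123. It covers setting variation as well as drop-out and belongs to the European study; no Dutch figure is given. Missingness and R² below are therefore assumptions.

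**Step 1: FMI as m grows.** Let W be the within-imputation and B the between-imputation variance. Under Rubin's rules:

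- r = (1 + 1/m)·B/W
- df = (m − 1)(1 + 1/r)²
- FMI = (r + 2/(df + 3))/(1 + r)

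As m increases, r tends to B/W and the df term vanishes, so FMI tends to B/(W + B). Example with B = 0.2, W = 0.8, m = 5: r = 1.2 × 0.25 = 0.30; df = 4 × (4.333)² = 75.1; FMI = (0.30 + 2/78.1)/1.30 = 0.250. The same formula gives:

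| True FMI | m = 5 | m = 20 | m = 100 | m = 1000 |
|---|---|---|---|---|
| 10 % | 12.4 % | 10.6 % | 10.1 % | 10.0 % |
| 20 % | 25.1 % | 21.2 % | 20.2 % | 20.0 % |
| 30 % | 37.5 % | 31.7 % | 30.3 % | 30.0 % |
| 40 % | 49.2 % | 42.2 % | 40.4 % | 40.0 % |

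The estimate falls a little with m, to a floor at the true value. With true FMI of 4.5 % it is 5.5 % at m = 5 and 4.98 % at m = 10, so there the rule does end.

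**Step 2: where the floor lies.** For a mean, with a proportion p missing completely at random and imputation predictors explaining a share R² of the outcome variance, limiting FMI = 1 − 1/[R² + (1 − R²)/(1 − p)].

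- p = 0.123: 0.123 at R² = 0; 0.089 at 0.3; 0.066 at 0.5; 0.040 at 0.7.
- R² = 0.3: 1 − 1/1.175 = 0.149 at p = 0.20; 1 − 1/1.30 = 0.231 at p = 0.30.

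The floor equals 0.05 when (1 − R²)·p/(1 − p) = 1/0.95 − 1 = 0.0526. That gives p of about 7 % at R² = 0.3, R² of about 0.62 at p = 0.123, and R² of about 0.79 at p = 0.20.

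**Step 3: simulation at the Dutch sample size.** Assumptions: N = 156, 1:1, one baseline covariate correlated 0.5 with the outcome and included in the analysis model, data missing completely at random, proper normal imputation, 60 replicates per level.

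| Missing | Mean FMI, m = 5 | m = 100 | m = 1000 | FMI ≤ 5 % at m = 5 | FMI ≤ 5 % at m = 1000 |
|---|---|---|---|---|---|
| 5 % | 6.6 % | 5.6 % | 5.5 % | 52 % | 45 % |
| 10 % | 11.9 % | 10.1 % | 10.1 % | 25 % | 2 % |
| 20 % | 25.0 % | 21.6 % | 20.8 % | 2 % | 0 % |
| 30 % | 35.9 % | 31.1 % | 30.8 % | 2 % | 0 % |
| 40 % | 44.0 % | 40.4 % | 40.3 % | 2 % | 0 % |

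From 10 % missing upwards, meeting the threshold at m = 5 is mostly noise in B. The covariate is already in the analysis model and adds nothing beyond it, so these figures sit near the R² = 0 case of Step 2.

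**Step 4: what m does control.** Loss of efficiency is about FMI/m. At FMI = 30 % and m = 20 it is 0.30/20 = 1.5 %, a relative efficiency of 1/1.015 = 0.985. A limit of 5 % on FMI/m needs m of at least 2, 4, 6 and 8 for FMI of 10, 20, 30 and 40 %. For the floors 0.089, 0.149 and 0.231 it needs only 2, 3 and 5.

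**The case against.** The strongest reply is that little turns on this. The sentence sets only the number of imputations in the economic evaluation. The imputation method, the pooling, the sample size and the mixed model under Clinical evaluation are untouched. An analyst who saw FMI level off would pick a sensible m, and by m = 20 the loss of efficiency is small. The article may also have meant loss of efficiency and shortened it. The point about impact stands and limits the severity. The point about intent is plausible, but it is an inference: the source cited for the rule is not at hand, and the words printed name FMI.

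A second reply is that FMI may be low here. QALYs are built from EQ-5D-5L scores at baseline and 3, 6 and 12 months, so participants who drop out may leave partial data that predict the rest well. This stands too. At 12.3 % missing, R² of 0.7 brings the floor to 0.040. The formula in Step 2 is also for a single mean, whereas the plan estimates adjusted between-arm differences from multilevel models, so its values are illustrative.

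Two stronger readings are tempting. A reader might infer that the rule can never be met. The documents do not support that, because it ends whenever true FMI is about 5 % or less, and they do not give what is needed to rule that out. A reader might also infer that the imputation model would be altered until FMI looked small, giving intervals that are too narrow. Nothing in the article suggests this; it states in advance the classes of variables in the imputation model and the use of predictive mean matching.

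**Conclusion.** The rule is wrong as written and should be corrected. Estimated FMI converges on B/(W + B), which the number of imputations does not change. If true FMI exceeds about 5 %, adding imputations does not meet the rule, except by chance at small m.

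That convergence follows from Rubin's rules and rests on no assumption about this trial. How far FMI would sit above 5 % does rest on assumptions: missingness, R² and data missing completely at random. Within the range shown the floor runs from 0.04 to 0.23, so the threshold is probably, but not certainly, out of reach. The 12.3 % should not be read as a Dutch drop-out rate.

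The effect is confined to the economic evaluation. The non-inferiority analysis is not affected, and the cost and effect estimates would change little if the analyst chose a reasonable m.

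**What to change.** Replace the sentence with wording such as: *Imputations will be added until the loss of efficiency, FMI/m, is at most 5 % for the cost, QALY and response differences, with a prespecified minimum number of imputations (e.g. 20) or a Monte Carlo error limit.*

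The second half is needed. By itself the FMI/m limit would allow as few as 2 to 5 imputations at FMI of 0.089 to 0.231, too few for stable variance estimates. Unlike the present rule, the new one can always be met by adding imputations. The cost is one sentence and slightly more computing.
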